## Methods and design

### Study design

This protocol describes a prospective longitudinal single-blind multicentre study, which will take place in 14 towns in the Netherlands. Recruitment will take place in two districts within a town, i.e.*, an intervention group* and *a control group*, that are matched based on social-economic status and population composition, and are enrolled through the town’s home care organization. Assignment of a district to the intervention or the control group will be done ‘a priori’. The intervention group will receive care of the healthcare professionals who participate in the implementation project ‘Don’t forget the mouth!’. The control group will receive care as usual. The participants will be visited at their home for assessment, at baseline, after 3, 6, and 12 months. The health care professionals of the intervention group will receive questionnaires. All data collection will be done by the same blinded researcher, viz., a dentist trained in the geriatric dentistry. Participants will be blinded. Health care professionals participate in the intervention, and therefore they cannot be blinded. The blinding code can be broken by the supporting investigator (RW) or principal investigator (FL) in case of a medical emergency of a participant. The Data Safety Monitoring Board (DSMB) is not needed because the risk for adverse side effects in this study is determined to be negligible. An independent monitor will monitor the study data according to ‘Good Clinical Practice’(GCP).

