### Sample size

The primary outcome variable is oral hygiene, determined by the proxy oral plaque, that will be classified according to the Silness and Loë index for dental plaque (DP) [29] and/or the Augsburger and Elahi index for dental prosthetic plaque (DPP) [30].

To calculate the sample size, a power of 80% was chosen (β = 0.20), with a significance level (α) of 0.05, expected standard deviation (σ) DP = 0.75 and DPP = 0.88 [3, 38]. For the intervention group, expected average scores were (μ^2^) DP = 1.63 and DPP = 1.60, for the control group the expected average scores were (μ^1^) DP = 2.17 and DPP = 2.13 [3, 38]. A clinically relevant effect of the intervention was set at an improvement of the oral hygiene with a DP and DPP reduction of 25% [3]. The sample size (*n*) was then calculated with the formula below [3].$$ n=\frac{2\upsigma 2}{\left({\upmu}^1-{\upmu}^2\right)2}\ f\ \left(\alpha, \beta \right) $$

To take non-parametric testing, drop-outs and loss to follow up in account, the sample size will be increased with 10% [9]. As a result, a sample size of *n* = 34 for DP and *n* = 49 for DPP would suffice.

This study will have intervention groups and control groups, and will take place in multiple towns and therefore is considered a multicentre study. With that in mind the sample size formula should be adjusted to the design effect (i.e.*,* the different towns that are participating).$$ Towns\ needed=\frac{2n\left(1+\left(m-1\right) ICC\right)}{m} $$

The expected intra class correlation is 0.03 [3, 38]. Based on a previous study [39], and the pilot study of ‘Don’t forget the mouth!’ (data not published), the expected number of participants (*m)* in each town is 20 in total, 8 for DP, and 12 for DPP. In total, at least 11 towns are needed in this study.

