### Statistical analysis

The personal data will be handled according the Dutch Personal Data Protection Act [40]. The data of each participant will be coded. The codes will be safeguarded by the coordinating investigator ([name]) and the principal investigator (FL). Data will be safely stored in the data management programme Castor EDC [41], and will be kept for 15 years [40]. Only the principal investigator (FL) and coordinating investigator ([name]) can fully access the final trial dataset.

Baseline comparisons between the intervention group and control group will be made using the Mann-Whitney U test. Oral hygiene will be compared at baseline, after 3, 6, and 12 months follow-up for the effect of time using the Friedman test, and the effect of group over time (intervention versus control) with the Kruskal Wallis test. The oral health and OHRQoL will also be analysed with the Mann-Whitney U test and the Kruskal Wallis test. Oral health care and the compliance of the health care professionals will be analysed according the constant comparative method of qualitative analysis [42, 43]. General health care and care dependency, will be assessed with descriptive statistics. The analysis will be conducted with IBM SPSS Statistics version 25, the level of significance will be 0.05. Protocol non-adherence is not applicable in this design. In case of missing data, imputation techniques will not be applied.

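### The planned between-arm tests treat participants as independent although whole matched districts form the arms, so the stated 0.05 level is not assured

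*Protocol article*

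**What the plan says.** **Design (Study design).** "Recruitment will take place in two districts within a town", one for each arm. The two districts are matched on socio-economic status and population composition, and each is assigned as a whole, in advance. The Discussion adds that districts could not be randomised. There are 14 towns, hence 28 districts.

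**Sample size.** The protocol recognises clustering: "With that in mind the sample size formula should be adjusted to the design effect". It describes this effect in terms of towns, takes an intraclass correlation (ICC) of 0.03, and expects that the number of participants "in each town is 20 in total, 8 for DP, and 12 for DPP". It concludes that at least 11 towns are needed.

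**Statistical analysis.** Baseline comparisons use the Mann-Whitney test. For oral hygiene, the primary outcome, change over time is given to the Friedman test and the comparison of the arms over time to the Kruskal-Wallis test. For oral health (OHAT) and quality of life (GOHAI): "The oral health and OHRQoL will also be analysed with the Mann-Whitney U test and the Kruskal Wallis test". The significance level is 0.05. No test carries a term for district, town or matched pair.

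**The concern.** The Mann-Whitney and Kruskal-Wallis tests derive their null distribution from participants who are independent of one another. Here participants in one district share home care workers, general practices and dental practices, and the intervention reaches them through those professionals. Some correlation within district is therefore plausible, and the sample size section itself expects correlation to inflate the variance. The analysis section drops it.

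The Friedman test allows for repeated measures on one person but still treats persons as independent. It is not a between-arm comparison, so the error rates worked out below do not apply to it.

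At stake is the meaning of the main p-value. If correlation lies within district, the tests reject too often. If it lies between towns, the tests fail to use the matching that the design set up.

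**Working it through.** **Inputs from the protocol.** "a power of 80% was chosen", "with a significance level (α) of 0.05"; standard deviations "DP = 0.75 and DPP = 0.88"; expected means 2.17 (control) and 1.63 (intervention) for dental plaque (DP), and 2.13 and 1.60 for prosthesis plaque (DPP); ICC 0.03; per town 8 DP, 12 DPP and 20 in total.

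**Assumptions.** Tests are two-sided (the protocol does not say, but only two-sided reproduces its figures). Participants divide equally between the two districts of a town, giving m = 4 (DP), 6 (DPP) and 10 (all participants) per district.

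**Step 1: the plan's own figures.** With f(α, β) = (1.960 + 0.842)² = 7.85:

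- DP: 2 × 0.75² / 0.54² × 7.85 = 30.28; divided by 0.9 = 33.65, so 34.
- DPP: 2 × 0.88² / 0.53² × 7.85 = 43.28; divided by 0.9 = 48.08, so 49.
- Towns, DP: 2 × 34 × (1 + 7 × 0.03) / 8 = 68 × 1.21 / 8 = 10.29, so 11.
- Towns, DPP: 2 × 49 × (1 + 11 × 0.03) / 12 = 98 × 1.33 / 12 = 10.86, so 11.

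All stated figures reproduce.

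**Step 2: variance of the arm difference.** Let ρd be the share of total variance between districts of the same town, and ρt the share between towns. Both arms are present in every town, so the town effect cancels from the difference in arm means. Relative to independent participants with the same total variance, the variance factor is

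V = m·ρd + (1 − ρd − ρt) = 1 + (m − 1)ρd − ρt.

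**Step 3: true error of an unadjusted test at nominal 5%.** Error = 2[1 − Φ(1.96 / √V)].

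| Where the 0.03 lies | DP, m = 4 | DPP, m = 6 | All, m = 10 |
|---|---|---|---|
| All within district | V = 1.09: 6.05% | V = 1.15: 6.8% | V = 1.27: 8.2% |
| 0.015 district, 0.015 town | V = 1.03: 5.4% (5.35) | V = 1.06: 5.7% | V = 1.12: 6.4% |
| All between towns | V = 0.97: 4.7% | V = 0.97: 4.7% | V = 0.97: 4.7% |

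**Step 4: check by simulation.** The Mann-Whitney test (the same as Kruskal-Wallis for two groups) was simulated in matched district pairs with normal data, 20,000 runs per scenario, for 11 and 14 towns. All within district: 5.8% for m = 4, 6.7–6.9% for m = 6, 7.6–8.1% for m = 10. Even split: 5.1–6.5% over the three sizes. All between towns: 4.6–4.9%. This agrees with the formula.

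**Step 5: a larger ICC (assumed, not in the protocol).** If the within-district ICC were 0.10, then V = 1.30, 1.50 and 1.90, and the error would be 8.6%, 11.0% and 15.5%.

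**Step 6: town count with district size in the design effect.** DP: 68 × 1.09 / 8 = 9.27. DPP: 98 × 1.15 / 12 = 9.39. Both round up to 10 towns.

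**The case against.** The strongest objection concerns direction. The protocol ties its design effect to towns, and every town holds both arms. Read literally, the 0.03 is a town correlation; it cancels between the arms, and the unpaired tests are slightly conservative. This stands. A reader might infer that the p-values are certainly too small, but the protocol gives no district-level correlation, so that holds only as far as correlation lies within district.

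A reader might also put the plan's own design effects of 1.21 and 1.33 into the error formula and obtain 7.5% and 8.9%. Those factors use the size of a whole town, whereas the unit assigned to an arm is a district of about half that size, so the figures do not describe this comparison.

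Nor does the sample size show a loss of power. Its design effect uses town size where district size fits the assignment, but the result is 11 towns instead of 10, and 14 are planned. This is a minor, conservative inconsistency.

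It may further be said that without randomisation a nominal 5% is not exact anyway, and that the Discussion admits possible selection bias. That is true, but it is a separate problem and no reason to add an avoidable one. An unseen statistical analysis plan is no full answer either: the protocol names the tests, so a later plan would have to repeat the fault or depart from the protocol.

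**Conclusion.** The point holds as a mismatch between design and analysis. The protocol allows for clustering when it sizes the study and ignores both clustering and pairing when it tests the arms, for the primary outcome as well as for OHAT and GOHAI.

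At the plan's ICC of 0.03 the effect is modest. For the two plaque outcomes the true error lies between about 4.7% and 6.8%; for outcomes on all participants it lies between about 4.7% and 8.2%. The upper ends require all the correlation to lie within district. The lower end requires a pure town effect, in which case the cost is lost precision from the matching. The figures rest on equal numbers per district and on the normal approximation, which the simulation supports.

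The omission itself is certain; its direction and size are not. This should be fixed, but it does not invalidate the study.

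**What to change.** Replace the between-arm tests for oral hygiene, OHAT and GOHAI with an analysis that respects district and town pair. Two options are equally acceptable:

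- a mixed model with a random effect for district, a town term and small-sample degrees of freedom; with repeated visits it also needs a participant effect;
- a paired analysis of district summaries over the 14 towns, for example a signed-rank test on the within-town differences, which keeps the non-parametric approach.

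State which is primary before the data are analysed. As a minor tidy-up, restate the design effect with district size (about 4 for DP and 6 for DPP) and note that the 11 towns are then conservative.

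The cost is a change of wording and one restated calculation. All the information needed, district and town of each participant, follows from the recruitment scheme. The downside is somewhat less favourable p-values if there is clustering within districts.

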### Intervention

The implementation project ‘Don’t forget the mouth!’ *(*i.e.*, the intervention)* aims to maintain and improve the oral health and the general health of community dwelling frail older people, with education and interdisciplinary collaborations. The collaborations of the health care professionals will be focused on of early recognition of decrease of daily oral hygiene care, oral health problems, and referral to colleagues if needed. Over the course of 12 months, health care professionals will attend four different meetings: two regional, and two national. The regional meetings will focus on the regional organisation of oral health care by interdisciplinary collaboration, the attitude towards oral health care, and oral health. The national meetings will focus on education about providing daily oral hygiene care, oral hygiene care for non-cooperative patients or clients, oral health, and professional oral health care.

Educational materials about daily oral hygiene care, oral health and professional oral health care have been developed for the participating health care professionals, informal caregivers, and all community dwelling frail older people, and will be available online (www.demondnietvergeten.nl). The intervention will also provide a screening-referral tool, which will be used by all health care professionals.

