### Secondary outcome variables

Secondary outcome variables are ‘oral health’, ‘oral health related quality of life’, ‘oral health care behaviour’, ‘general health and care dependency’, and ‘compliance of the health care professionals’.

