#### General health and care dependency

General health and care dependency will be measured with The Older People and Informal Caregiver Survey Minimum Data Set (TOPICS-MDS) questionnaires [36], at baseline and after 12 months. These questionnaires are part of a larger national initiative to assess the Dutch senior population [36]. There are two questionnaires, one for the older person and one for the informal care giver. The questionnaire at baseline for the participant contains 51 items, the follow-up questionnaire contains 46 items; both are about demographics, morbidity, quality of life, functional limitations, emotional wellbeing, social functioning, and health service utilization [37]. The questionnaire at baseline for the informal care giver contains 27 items, the follow-up questionnaire contains 26 items; both are about demographics, hours of informal care, and quality of life [37].

Only the data collected with items about demographics, morbidity, health service utilization, and hours of informal care will be analysed in the current study to describe the population and compare the general health and care dependency between the intervention group and the control group.

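### General health and care dependency is to be compared between the groups, but the descriptive-only analysis gives no baseline-adjusted 12-month difference and no interval to support a between-group statement

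*Protocol article*

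**What the plan says.** The Secondary outcome variables section gives the status of this outcome: "Secondary outcome variables are ‘oral health’, ‘oral health related quality of life’, ‘oral health care behaviour’, ‘general health and care dependency" (the list ends with compliance of the professionals).

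The General health and care dependency section measures it with the TOPICS-MDS questionnaires "at baseline and after 12 months". Of the items collected, only those on demographics, morbidity, health service utilization and hours of informal care are to be analysed. They have two purposes: to describe the population, and to "compare the general health and care dependency between the intervention group and the control group".

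The Statistical analysis section assigns one method: "General health care and care dependency, will be assessed with descriptive statistics". Two other sentences in that section bear on this:

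- "Baseline comparisons between the intervention group and control group will be made using the Mann-Whitney U test". This is not limited to particular variables, but it concerns baseline only.
- "The oral health and OHRQoL will also be analysed with the Mann-Whitney U test and the Kruskal Wallis test". This covers two other secondary outcomes and not this one.

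The Intervention section says that the project "aims to maintain and improve the oral health and the general health of community dwelling frail older people". The abstract says that effectiveness will be determined with oral hygiene, the primary outcome.

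**The concern.** A comparison of the groups is one of the two stated uses of these data, yet no method is named that estimates a difference between them at 12 months. This is not detail left to an analysis plan: the article names a method, and an analysis plan that followed it would inherit the gap.

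The design makes the gap matter. Districts are assigned in advance, the Discussion says that they could not be randomised and concedes possible selection bias, and the Sample size section allows for correlation within towns. Two columns of 12-month summaries then mix any effect with baseline differences and with chance variation between districts. The baseline values are collected, but no planned step uses them to adjust the 12-month comparison.

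At stake is what can be said about general health. A visible difference could be taken for benefit, or similar columns for absence of effect, and the planned output would not show whether the data support either reading.

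**Working it through.** **1. The text, side by side.**

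| Step | Section | Content |
|---|---|---|
| Status | Secondary outcome variables | listed secondary outcome |
| Data | General health and care dependency | baseline and 12 months |
| Purpose | General health and care dependency | describe the population; compare the groups |
| Baseline method | Statistical analysis | Mann-Whitney U, all baseline comparisons |
| 12-month method | Statistical analysis | descriptive statistics |

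Baseline imbalance would be visible. A 12-month difference would have no adjusted estimate and no interval.

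**2. The plan's own figures.** None is given for this outcome. Those for the primary outcome reproduce and are not in dispute. The plan's formula is n = 2σ²/(μ1 − μ2)² × f, with f = (1.960 + 0.842)² ≈ 7.85 for "a power of 80% was chosen (β = 0.20), with a significance level (α) of 0.05" (two-sided).

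- DP: 2 × 0.75²/0.54² × 7.85 = 30.3, rounded up to 31; × 1.1 = 34.1 (stated 34).
- DPP: 2 × 0.88²/0.53² × 7.85 = 43.3, rounded up to 44; × 1.1 = 48.4, rounded up to 49 (stated 49).
- Towns: DP 2 × 34 × (1 + 7 × 0.03)/8 = 10.3; DPP 2 × 49 × (1 + 11 × 0.03)/12 = 10.9; hence 11 (stated 11).

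**3. Illustrative precision for this outcome.** From the article: 11 towns needed, 14 planned, 20 participants per town, ICC 0.03. Assumptions: participants split equally between the two districts; the ICC, given for plaque, carried over to these items; complete data apart from the stated loss, which is either nil or 10% (the article's 10% increase also covers non-parametric testing).

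Formulas: design effect DE = 1 + (m − 1) × 0.03; effective n per arm = n/DE; 95% half-width in SD units = 1.96 × √(2/effective n). The cluster size m is taken first as the district, then as the whole town, as in the plan's own formula.

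| Towns | Loss | n per arm | m | DE | Effective n | Half-width (SD) |
|---|---|---|---|---|---|---|
| 14 | none | 140 | 10 (district) | 1.27 | 110.2 | 0.26 |
| 14 | 10% | 126 | 9 (district) | 1.24 | 101.6 | 0.28 |
| 14 | none | 140 | 20 (town) | 1.57 | 89.2 | 0.29 |
| 14 | 10% | 126 | 18 (town) | 1.51 | 83.4 | 0.30 |
| 11 | none | 110 | 10 (district) | 1.27 | 86.6 | 0.30 |
| 11 | 10% | 99 | 9 (district) | 1.24 | 79.8 | 0.31 |
| 11 | none | 110 | 20 (town) | 1.57 | 70.1 | 0.33 |
| 11 | 10% | 99 | 18 (town) | 1.51 | 65.6 | 0.34 |

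With ICC 0 and no loss the half-width is 0.23 (14 towns) or 0.26 (11 towns). For a yes/no item in the second row, 1.96 × √(2p(1 − p)/101.6) gives 11 percentage points at p = 0.2 and 14 at p = 0.5.

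These figures show that an interval is feasible and about how wide it would be. They do not measure an error in the plan. They use a normal quantile, which is optimistic with 11 to 14 towns. They also ignore both the matching of districts within towns and the gain from baseline adjustment, either of which could narrow the interval.

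**The case against.** A reader might infer that the two sections contradict each other. They do not. The outcome section promises to describe and to compare, without mentioning a test, an estimate or an interval. Summaries by group at two time points are a comparison in a loose sense.

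A reader might also infer that half of the study's own aim goes unanalysed. The documents do not support that either. Improving general health is an aim of the implementation project for frail older people. The study assesses the project's effectiveness, and the abstract ties that to oral hygiene. Nowhere does the article say that a general-health effect will be concluded, or that a difference between two columns will be reported as one.

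Descriptive reporting of a multi-item secondary outcome that was not powered is an ordinary, cautious choice, and it limits the number of tests. Baseline imbalance would not be hidden, because the baseline Mann-Whitney comparisons can cover these items, and descriptive statistics would normally include spread and counts.

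The contrast with the tested outcomes is also weaker than it looks. The Mann-Whitney and Kruskal-Wallis tests named for them, as written, give no baseline-adjusted estimate, no interval and no allowance for clustering either.

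All of this stands, and it limits the weight of the point. What remains is narrower. Seeing a baseline imbalance is not the same as allowing for it, and within-group spread is not an interval for a difference between clustered groups. If the comparison announced in the outcome section is meant to say anything about the groups at 12 months, the named method cannot carry it.

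**Conclusion.** The point holds as an inexpensive improvement to a secondary analysis: the named method is too weak for one of its two stated uses. It is not a contradiction, and it leaves the primary conclusion unaffected. As written, the plan can describe the two groups but cannot support a statement that they differ, or do not differ, in general health or care dependency at 12 months.

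Its scale can only be illustrated: an unadjusted 95% half-width of roughly 0.26 to 0.34 SD across 11 to 14 towns, with or without 10% loss. That rests on 20 participants per town split equally and on a plaque ICC applied to morbidity, service use and care hours, for which the article gives no value. Differences within that range would be compatible with no difference, and the planned summaries would not show it.

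**What to change.** In the Statistical analysis section, keep descriptive statistics for demographics and for describing the population. For morbidity, health service utilization and hours of informal care, add the between-group difference at 12 months, adjusted for the participant's own baseline value. Give a 95% CI that allows for district within town and for the small number of towns. Use a method suited to skewed or binary items, and label the results exploratory.

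If the sponsor prefers description only, the outcome section and the Statistical analysis section should both say so, and should state that no conclusion on a general-health effect will be drawn.

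The first option costs a sentence or two and a few model fits on data that are to be collected anyway. Its small downside is a few more secondary estimates, which the exploratory label covers. The second option costs wording only.

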### Participants

The inclusion criteria are: community dwelling people aged 65 years or older; a Mini Mental State Examination (MMSE, a short screening instrument which assesses general cognition, awareness, and memory [22]) score between 18 and 24, which in this study will be considered indicative of dementia [23, 24], and receiving care from health care professionals of the participating home care organization and general practice. Exclusion criteria are: suffering from a terminal illness; having a MMSE score lower than 18 or higher than 25; and being edentulous without prosthesis. Additionally, the participants in the control group will be excluded if they are registered at the general or dental practice of the intervention group.

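### With no imputation, the Friedman test drops anyone who misses a visit and the Kruskal-Wallis test, if run per visit, uses only those still observed, so loss that differs by arm may bias the group comparison

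*Protocol article*

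**What the plan says.** The Study design section sets four assessments: "The participants will be visited at their home for assessment, at baseline, after 3, 6, and 12 months". The Statistical analysis section then fixes three things for the primary outcome.

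- Time effect: "Oral hygiene will be compared at baseline, after 3, 6, and 12 months follow-up for the effect of time using the Friedman test".
- Group effect: "the effect of group over time (intervention versus control) with the Kruskal Wallis test". The article does not say whether this test is applied at each visit, to change scores, or to a summary over visits.
- Missing data: "In case of missing data, imputation techniques will not be applied".

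The Participants section describes the population as aged 65 or older, living in the community, with an MMSE "score between 18 and 24, which in this study will be considered indicative of dementia". The Discussion says that the districts could not be randomised. The Sample size section makes one allowance for several losses together: "To take non-parametric testing, drop-outs and loss to follow up in account, the sample size will be increased with 10" per cent. No section gives an expected dropout rate by reason or by arm.

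**The concern.** Declining imputation is not an error in itself, because a likelihood-based longitudinal model needs none. The weakness is the combination of that rule with these two tests.

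The Friedman test works on complete blocks. A participant seen at baseline, 3 and 6 months but not at 12 months contributes nothing to the time analysis, although three scores were recorded. A Kruskal-Wallis test run at each visit keeps more records, but it compares whoever remains, a set that changes from visit to visit. It makes no use of the earlier plaque scores of those who left.

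The article itself gives reasons to expect loss related to health. Its Background links poor oral health to pneumonia, poorly regulated diabetes, cardiovascular disease and cognitive decline. Participants are followed for a year by home visit and may withdraw at any time. Arms are formed by district without randomisation, and the professionals know the allocation, so loss could also differ between arms. In that case the comparison on which the effectiveness claim rests could be shifted, and neither planned test would correct it.

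**Working it through.** **1. The plan's own figures.** Inputs from the Sample size section: SD 0.75 (DP) and 0.88 (DPP); means 2.17 v 1.63 and 2.13 v 1.60; power 80% and α 0.05, taken as two-sided, so f = 7.849.

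- DP: 2 × 0.75² / 0.54² × 7.849 = 30.28; divided by 0.9 = 33.6, so 34.
- DPP: 2 × 0.88² / 0.53² × 7.849 = 43.28; divided by 0.9 = 48.1, so 49.
- Towns: 2 × 34 × (1 + 7 × 0.03) / 8 = 10.29, and 2 × 49 × (1 + 11 × 0.03) / 12 = 10.86, so 11.

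These agree with the stated 34, 49 and 11. The plan gives no figure for incomplete follow-up beyond the shared 10%.

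**2. Who remains in the Friedman test.** Let p be the probability of missing a follow-up visit. This is assumed, because the documents give none. With three follow-up visits missed independently, the share with all four visits is (1 − p)³.

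| p (assumed) | Complete at all four | Dropped from the time analysis |
|---|---|---|
| 5% | 0.857 | 14% |
| 10% | 0.729 | 27% |
| 15% | 0.614 | 39% |

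The same formula holds for permanent dropout if p is the share lost in each interval. If instead the same people miss every follow-up visit, the share dropped is only p.

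**3. What loss can do to the group difference.** An illustrative simulation used 200,000 participants per arm. Its DP figures came from the plan: control mean 2.17, SD 0.75, difference 0.54 at every follow-up. Everything else was assumed:

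- within-person correlation 0.5;
- permanent loss in each interval with log-odds −2.0, plus 0.7 per SD of the previous plaque score where loss is plaque-related;
- a further 5% of follow-up visits missed at random.

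About 55% to 62% were complete at all four visits, so the assumed loss is heavy.

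| Loss mechanism | Difference at 12 months, no loss | Those seen at 12 months | Four-visit completers |
|---|---|---|---|
| Unrelated to plaque | 0.538 | 0.539 | 0.539 |
| Plaque-related, same in both arms | 0.542 | 0.523 | 0.523 |
| Plaque-related, control only | 0.545 | 0.444 | 0.444 |
| Plaque-related, intervention only | 0.542 | 0.616 | 0.617 |

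The shifts among those seen are (0.523 − 0.542) / 0.542 = −4%, (0.444 − 0.545) / 0.545 = −19% and (0.616 − 0.542) / 0.542 = +14%. The two right-hand columns agree to within 0.001. So keeping everyone seen at 12 months does not remove the shift. Loss here depends on the previous score, which is observed in most cases and which neither rank test uses.

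**The case against.** The strongest reply is that the complete-block problem belongs only to the secondary question. The protocol confines the Friedman test to the time effect ("for the effect of time using the Friedman test"), while effectiveness is judged with the Kruskal-Wallis test, which needs no complete blocks. This stands. A reader might infer that the whole analysis shrinks to completers. The documents support that only for the time effect; it would extend to the group test only if that test were run on a summary needing all four visits, which the article does not say.

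Three further readings go beyond the documents.

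- **That the remaining participants are healthier and the comparison is biased.** No section reports dropout reasons, direction or a difference by arm. The simulation shows no bias when loss is unrelated to plaque, and little when the mechanism is the same in both arms.
- **That the tests are valid only if data are missing completely at random.** This is too strong. Loss that depends on arm alone does not distort a between-group rank test, and under the null the test keeps its validity when one mechanism acts in both arms.
- **That the 10% allowance leaves the trial short of power.** The Discussion sets 14 planned towns against 11 needed, as margin for withdrawals. Assume a rank-test efficiency of 0.955. For DP, 14 towns give 14 × 8 / 2 = 56 per arm; 56 / 1.21 = 46.3 effective, against 30.28 / 0.955 = 31.7 needed, which leaves room for about 31% attrition. For DPP, 84 / 1.33 = 63.2 against 43.28 / 0.955 = 45.3 leaves about 28%.

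It may also be said that handling of missing data belongs in an analysis plan that is not shown. That is fair for a sensitivity analysis, whose absence from the article is not a fault. It does not cover the rule and the tests, which the article states outright.

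**Conclusion.** The point holds in a limited form. The stated combination of no imputation, a complete-block test for time and a rank test for group makes no use of earlier scores from those who leave. Two consequences follow.

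- **Certain in kind, unknown in size:** the Friedman test discards observed data from anyone with a missed visit. The loss is 14% to 39% of participants for assumed independent missed-visit rates of 5% to 15%, and less if the same people miss repeatedly.
- **Possible, not shown:** the group comparison may be shifted, in either direction, mainly if plaque-related loss differs by arm. The shifts of −19% and +14% rest on heavy assumed loss confined to one arm. They show what could happen and do not predict it.

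This is a choice of a weaker method where a better one is at hand. The sample size and the number of towns are not affected.

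**What to change.** Make the primary analysis of DP and of DPP a likelihood-based mixed model on all observed visits. Include group, visit, group-by-visit and baseline score, with random effects for participant and for district within town, and baseline MMSE as a covariate. The district effect matters because allocation is by district and the Sample size section already recognises clustering. The model is valid under missing at random and needs no imputation, so the sentence on imputation can stay.

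Keep the Friedman and Kruskal-Wallis tests as supportive analyses, and state how the latter is applied across visits. Add one sensitivity analysis that shifts unobserved scores by amounts chosen separately for each arm, with deaths handled separately from missed visits.

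The cost is a distributional assumption for the plaque scores, which should be checked on the residuals, and a little more analysis work. No new data are needed, since the plaque scores and MMSE are already collected.
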